#### Implementation process outcomes

We will conduct an integrated process evaluation using a mixed-methods approach, including semistructured interviews, focus group discussions, surveys, documentary analysis and direct observations. Guided by NPT, this evaluation will explore how implementers engage with the selected implementation strategies and how contextual factors influence their efforts to drive improvement. Specifically, we will examine the extent to which the strategies are delivered as intended (fidelity of delivery), how they are understood and accepted by recipients (fidelity of receipt), and how they are applied in practice (fidelity of enactment). This approach will allow us to assess the mechanisms through which the intervention becomes embedded in routine practice and identify factors that facilitate or hinder its normalisation.

#### Data collection

We will construct a longitudinal cohort of patients with T2D in both arms, enrolling patients before implementation and following them for 12 months for outcome assessment and an additional 6 months for sustainability assessment. Our methodology builds on the e-Cohort framework that we previously optimised and used for this context at the provincial level.^34^ Participants will be contacted via telephone or in person at the PHC centre for eligibility assessment. If eligible, they will have their first in-person visit at their PHC centre, during which informed consent will be requested for recruitment (onlinesupplemental materials A  B). For all consenting patients, we will extract data about patient visits and laboratory testing from routine clinical records and costs from administrative databases for all participating facilities. During the first visit, we will administer a baseline questionnaire. Subsequently, we will conduct quarterly telephone surveys and conclude with an endline questionnaire in person at the end of the intervention period. We will implement a standardised clinical electronic data collection system using REDCap for all study data collection phases. The research team will collect monitoring data from participating facilities throughout the trial. This includes attendance at QILN activities (total attendance and sustained participation by initial team members), team meetings within each facility, timely submission of implementation team reports and implementation checklists completed quarterly during the study team observations. Specially trained data collectors will perform daily data processing at each participating PHC centre.

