Type 2 diabetes mellitus (T2D) is an increasing global health burden. In 2019, diabetes was the direct cause of 1.5 million deaths worldwide.^10^ In addition to the cost of treatment for T2D and its complications, which is a significant burden for national health services, T2D and other NCDs heavily impact productivity, particularly concerning lost or reduced working days due to illness.^11^ Central and South American countries spend an average of 18.4% of their total health expenditure on diabetes.^12 13^ Diabetes detection and control are primarily the responsibility of the non-private schemes.^14 15^ To date, Argentina’s PHC system has failed to meet this challenge; T2D detection and control coverages are low, and those in treatment often bypass PHC for secondary facilities.^16^ Of the estimated 12.7% of the national population living with T2D, only 50% are aware of living with their diagnosis, and only 40% of these individuals have achieved metabolic control (HbA1c <7%), leaving 80% of cases uncontrolled.^17 18^

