The Quality Evidence System Transformation Network (QuEST Network) provides policymakers with evidence and tools for health system improvement. QuEST-Latin America and the Caribbean leads regional research and dissemination.^19^ Collaboration with the government of the Argentinian province of Mendoza led to efforts to address post-COVID-19 health challenges. Together, we conducted a comprehensive assessment of PHC system quality, focusing on NCDs and patient experience. This diagnostic assessment included a population-based survey of 1220 respondents, a cohort study of patients with diabetes, analysis of routine health data to identify care patterns and disease control, and qualitative studies of how NCD patients use PHC services and how providers interact with these patients.^16 20^ Our analysis from this diagnostic process showed significant deficits in patient experience, system competence and trust in the public health system. The study found that accessing care was difficult due to appointment difficulties and long waiting times, and obtaining medication and laboratory tests at secondary centres was also problematic. Financial constraints were significant, with co-payments in the social security sector, transportation costs and lost work revenue. Strategies employed included networking, emergency service use, careful planning and taking loans.^16^ We also conducted a Delphi consensus process with local stakeholders to identify specific recommendations, based on the findings of the diagnostic studies, to improve healthcare services.^21^ Based on this diagnostic process and our established relationship with policymakers and stakeholders in the province of Mendoza, we propose to codesign a new model of care to be tested and evaluated in a pragmatic cluster randomised controlled trial to improve health for individuals with diabetes in Argentina.

In this protocol, we conceptualise the redesigned PHC model itself—built around the national clinical guideline for T2D management—as the core intervention. Our trial tests a package of implementation strategies designed to embed this guideline-based model into everyday practice.

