### Phase II: trial deployment

#### Setting

The trial will be implemented in PHC centres across the province of Mendoza, Argentina, which serve approximately 45% of the population, primarily individuals from socioeconomically disadvantaged backgrounds. The province is administratively divided into 18 departments. The unit of randomisation (cluster) will be the department. 12 departments will be selected, each contributing at least two PHC centres. Clusters will include two or three PHC centres providing care to ≥50 individuals diagnosed with T2D per cluster. Centres involved in the pilot phase will be excluded from phase II.

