#### Outcomes

The primary outcome will be a composite outcome including glycaemic control (HbA1c <8%); blood pressure control (<140/90 mm Hg); and use of statins (statin prescription) limited to patients ≥40 years. The source to obtain this data will be routine clinical records.

Secondary outcomes measured through participant questionnaires include user-reported quality of care (key secondary outcome), PHC engagement, system competence, patient confidence in the health system, inequities in outcomes and patient empowerment. User-reported Quality of Care is the overall rating of quality of care from enrolled patients, categorised as ‘excellent or very good’ versus ‘good’ or worse. PHC engagement is measured as the percentage of visits conducted at the PHC level during the data collection period, with positive engagement defined as ≥75% of all non-urgent ambulatory visits.^31^ System competence is defined as ≥75% of enrolled patients per site adhering to the complete set of selected diabetes prevention recommendations from national and provincial guidelines: annual eye exam, yearly foot exam, annual kidney function assessment, annual blood pressure measurement and biannual HbA1c measurement during the follow-up period. Patient confidence in the health system is measured by the combination of three aspects in the e-Cohort survey: health security, endorsement of the current system and trajectory.^32^ Security: We will calculate the percentage of respondents answering ‘somewhat’ or ‘very confident’ to ‘How confident are you that you would receive good quality healthcare if you became very sick?’ and ‘that you could afford the healthcare you needed if you became very sick?’. Confidence: The proportion of respondents indicates that in the past 2 years, the health system has been improving (vs staying the same or getting worse). Endorsement is indicated by agreement that the system works well and needs only minor reforms (vs significant changes needed or need to be completely rebuilt). To assess inequities, we will explore gender, migration status, education and income as potential variables related to underperformance in primary outcomes. Finally, we will measure patient empowerment using the Diabetes Empowerment Scale. This instrument is free and easy to use and has been adapted and validated in its Spanish version.^33^

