We will use multiple approaches to address missing data. For clinical outcomes, those with missing outcome data will be considered as not achieving the composite outcome for primary analyses, given the lack of evidence of disease control. We will conduct a sensitivity analysis using inverse probability weights calculated from clinical and participant data to reweight the complete data sample to the total patient population. Inverse weights provide valid estimates of the full sample estimate if the assumption of missing at random is met. We will apply the same approach for secondary outcomes. Based on experience with the eCohort methodology, we anticipate high response rates and largely complete responses within the survey. In the event of greater than anticipated missingness within surveys (eg, skipped items), we will conduct an additional analysis using multiple imputation approaches to robustly impute missing responses.^36^

Planned subgroup analyses will explore the potential differential effects of the intervention by gender, migrant status, income and educational level (effect modifiers). This will indicate whether the intervention contributes to reducing inequalities in care. Subgroup analyses will be exploratory. To evaluate inequalities, we will estimate the slope index of inequality and the absolute gradient of inequality across income groups and educational attainment to quantify the absolute inequality in each outcome within the sample in each arm. All analyses will be performed using R V.4.3.1^37^

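### The record sources for the primary composite are not shown to reach beyond the participating PHC centres; with missing scored as failure, a shift of care into PHC can raise the composite with no change in disease control

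*Protocol article*

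**What the plan says.** All references are to the protocol article.

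- **Source of the outcome.** For the composite of HbA1c, blood pressure and statin prescription, Outcomes states: "The source to obtain this data will be routine clinical records". It names no level of care.
- **Extraction.** Data collection states: "we will extract data about patient visits and laboratory testing from routine clinical records and costs from administrative databases for all participating facilities". Blood pressure and statins are not named in that sentence. The same section adds: "Specially trained data collectors will perform daily data processing at each participating PHC centre".
- **What a participating facility is.** Setting states: "Clusters will include two or three PHC centres providing care to ≥50 individuals diagnosed with T2D per cluster".
- **Care outside PHC.** The Introduction says that "those in treatment often bypass PHC for secondary facilities", and reports from the diagnostic phase that "obtaining medication and laboratory tests at secondary centres was also problematic".
- **Missing data.** In Data analysis, "those with missing outcome data will be considered as not achieving the composite outcome for primary analyses". As a supplement: "We will conduct a sensitivity analysis using inverse probability weights calculated from clinical and participant data".
- **Place of care as a target.** Aims lists service use patterns among the things the model should affect. Outcomes makes the PHC share of visits a secondary outcome, positive at 75% or more of non-urgent ambulatory visits. Ethics and dissemination anticipates less use of secondary and tertiary facilities.

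**The concern.** These statements interact. If an HbA1c result or a prescription made at a secondary facility does not reach the records that are searched, the patient is scored as not achieving the composite, whatever the true state of control. A model that brings visits back to PHC would also bring the evidence of control into view. The between-arm contrast then adds together two things: better control, and better visibility of the same control.

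The second part would favour the intervention, and would be largest where the model succeeds in moving care. Adjusting for baseline does not remove it, because the change in capture happens after randomisation. At stake is whether a positive primary result can be read as improved disease control, which is the primary objective.

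**Working it through.** **1. The plan's own figure.** Inputs from Sample size: 30% against 50%, two-sided 5%, six clusters per arm, ICC 0.05, cluster autocorrelation 0.5, individual autocorrelation 0.6, 26 per cluster before attrition.

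- Clustering factor: 1 + 25 × 0.05 = 2.25.
- Baseline–follow-up correlation of cluster means: r = (26 × 0.05 × 0.5 + 0.95 × 0.6) / 2.25 = 0.542.
- Design effect: 2.25 × (1 − 0.542²) = 1.588.
- SE = √[(0.21 + 0.25) × 1.588 / 156] = 0.0684, and 0.20 / 0.0684 = 2.92.
- Power is 79.7% with t on 22 df (24 cluster-periods minus 2).
- Attrition: 26 / 0.8 = 32.5, rounded up to 33; 33 × 12 = 396.

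The sample size reproduces and is not in question.

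**2. Model for the artefact.** Let p be the true composite rate, the same in both arms. Let c0 and c1 be the shares of patients with a complete captured record in control and intervention, with capture unrelated to control. Because missing counts as failure, the observed rate in each arm is p × c, so

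false difference = p × (c1 − c0).

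The protocol gives no capture rate. All values of c below are assumptions.

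**3. Size per 10 points of extra capture.** p = 0.30 gives 0.30 × 0.10 = 3 points; p = 0.50 gives 0.50 × 0.10 = 5 points. A gain of 20 points gives 6 to 10 points, which is 30% to 50% of the 20-point target.

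**4. A worked case.** Take p = 0.40 and c0 = 0.75, so the observed control rate is 0.40 × 0.75 = 30%, equal to the planning rate. The test is a cluster-level comparison at follow-up with 33 per cluster, ICC 0.05 and 10 df. The variance factor is 1 + 32 × 0.05 = 2.6, and SE = √[(q0(1 − q0) + q1(1 − q1)) × 2.6 / 198], where q0 and q1 are the observed rates.

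| Capture, intervention | Observed rates | False difference | SE | Significant with no true effect |
|---|---|---|---|---|
| 85% | 30% v 34% | 4 points | 0.0755 | 7.7% |
| 90% | 30% v 36% | 6 points | 0.0760 | 11.0% |
| 95% | 30% v 38% | 8 points | 0.0765 | 15.8% |

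The nominal figure is 5%.

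**5. Upper bound.** Suppose the planned 30% already contains missing-as-failure. Then p = 0.30 / c0, and the largest artefact, at c1 = 100%, is 0.30 / c0 − 0.30. For c0 of 90%, 80%, 70% and 60% this is 3.3, 7.5, 12.9 and 20 points. Under this assumption, an artefact of the full target needs control capture of 60% or less.

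**6. What weighting does.** Under the same model, captured patients show p in both arms (40% v 40% in the worked case). An analysis of captured patients, weighted within arm, is therefore unbiased. Bias returns if capture also depends on control status through something not measured. The primary analysis is not weighted, so steps 3 to 5 apply to it in full.

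**The case against.** The strongest reply is that the protocol never says extraction stops at PHC. That is correct. In the Data collection sentence the closing phrase on participating facilities may attach only to the cost databases, and Outcomes does not restrict routine records by level of care. A reader might infer that PHC charts are the only source, but this is an inference: the natural one, since the sites are PHC centres and the data collectors work there, yet not stated.

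A reader might also infer that tests and medicines are generally obtained at secondary centres and never seen at PHC. The Introduction does not support that. It reports difficulty in obtaining them there, gives no share, and does not say that results fail to return to the PHC chart. The statin component is prescription, so the place where the medicine is collected is irrelevant if PHC prescribes it. Study participants must also receive care at a participating centre, which limits bypass in this cohort. It does not exclude tests or prescriptions elsewhere: a patient counted as engaged may still have up to a quarter of non-urgent visits outside PHC.

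It is also fair to say that weighting can repair the problem under the model used here, and that place of care is to be measured. A claim that weighting cannot help would be wrong. What stands is that weighting is only a sensitivity analysis and rests on missing at random.

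Finally, Data analysis already promises counts of complete and incomplete records. That helps, but it does not commit to a breakdown by component and source. A condensed article may leave the list of record systems to the full protocol. Here, though, the source and the missing-as-failure rule are both stated, and it is their combination that can bias the primary contrast.

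**Conclusion.** The concern holds as a risk of differential ascertainment in the primary analysis, not as a demonstrated bias. It needs two conditions, neither documented: some secondary-level results do not reach the extracted records, and capture rises more in the intervention arm than in control. If both hold, the direction favours the intervention, and each 10 points of extra capture is worth 3 to 5 points for true rates of 30% to 50%, against a target of 20. The rejection rates in the worked case are illustrations resting on an assumed 75% capture in control. That the composite will rise through record capture alone is a stronger statement than the document supports; it can rise. If the records searched already hold secondary-level results for both arms, the point is settled by saying so. This should be resolved before endline extraction; confidence is moderate.

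**What to change.** - **Data collection:** state that HbA1c, blood pressure and statin prescription are taken for every enrolled patient from PHC records and from accessible secondary-level public records, by the same procedure in both arms.
- **Endline questionnaire (already planned, in person):** add items on where tests were done and prescriptions issued, and use the answers in the weights.
- **Data analysis:** report capture of each component by arm and by source.
- **If secondary-level records cannot be reached:** define the primary outcome as control documented at PHC, and draw no conclusion on disease control unless the weighted analysis agrees.

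The cost is a data-access request, a few questionnaire items and some extraction time for at most 396 consenting patients. The team has already analysed routine health data in the province (Introduction). The fallback needs a change of wording only. The sample size is unaffected.

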### Phase III: analysis and reporting

#### Objectives

The objectives of this phase are (1) to evaluate the effectiveness of the intervention and its sustainability, (2) to report findings and (3) to engage stakeholders in disseminating results and translating their results to public policy.

#### Procedures

Procedures in this phase will include (a) Analysis of findings: Once the data management team closes the database, we will conduct the analysis plan as described below, (b) Report on study results: The main manuscripts on the different study phases will be written and sent out for peer review before the closure of the grant period. Engagement of policymakers through workshops will be conducted to interpret results in context. See more in dissemination below, (c) Control arm clusters will receive the intervention, if proven effective, after the study follow-up period, but prior to the completion of data analysis and (d) Communicate study results to stakeholders to promote policy adoption.

#### Data analysis

We will use all available data from all randomised clusters and conduct all analyses on the intention-to-treat (ITT) population, including all clusters and patients in the randomised group, regardless of intervention adherence. Summary statistics will be given for baseline data by treatment group using means, SD, medians, minimum, maximum and quartiles for continuous variables and counts and percentages for categorical variables. We will quantify complete vs incomplete records and describe the characteristics of patients lost to follow-up.

For the composite clinical outcome, the primary ITT analysis will compare the proportion of patients achieving an HbA1c level <8%, blood pressure control <140/90 mm Hg and statin uptake between the trial arms at the end of the study. We expect a good covariate balance between the groups; therefore, the ITT analysis will be performed by comparing proportions. Patient and cluster-level covariates can be included in a mixed-effects logistic regression model to account for the cluster effect and obtain an adjusted estimate of the average treatment effect for within-cluster change.^35^ Adjusted ORs will be reported with 95% CIs, p values and ICCs will be reported to estimate the percentage of variance explained by each level.

For quality of care, we will compare the proportion of patients reporting overall quality of care as ‘excellent’ or ‘very good’ before and after the intervention phase between trial arms using difference-in-difference regression analysis to estimate the average treatment effect. Engagement and confidence in the health system will be evaluated by comparing the proportion of patients achieving the expected threshold in each trial using a χ^2^ test for proportions. Fisher’s exact test will evaluate system competence across participating PHC centres. Direct costs related to diabetes care will be reported for each group. We may expect higher costs in the intervention group due to increased and better utilisation of health services. The mean cost will be analysed considering the variable distribution (non-normal/normal). For all outcomes, we will conduct mixed effects regression adjusted for covariates and clustered by department to provide an average treatment effect for expected change in outcomes within each department.

We will use multiple approaches to address missing data. For clinical outcomes, those with missing outcome data will be considered as not achieving the composite outcome for primary analyses, given the lack of evidence of disease control. We will conduct a sensitivity analysis using inverse probability weights calculated from clinical and participant data to reweight the complete data sample to the total patient population. Inverse weights provide valid estimates of the full sample estimate if the assumption of missing at random is met. We will apply the same approach for secondary outcomes. Based on experience with the eCohort methodology, we anticipate high response rates and largely complete responses within the survey. In the event of greater than anticipated missingness within surveys (eg, skipped items), we will conduct an additional analysis using multiple imputation approaches to robustly impute missing responses.^36^

Planned subgroup analyses will explore the potential differential effects of the intervention by gender, migrant status, income and educational level (effect modifiers). This will indicate whether the intervention contributes to reducing inequalities in care. Subgroup analyses will be exploratory. To evaluate inequalities, we will estimate the slope index of inequality and the absolute gradient of inequality across income groups and educational attainment to quantify the absolute inequality in each outcome within the sample in each arm. All analyses will be performed using R V.4.3.1^37^

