### Design

This study is a pragmatic, parallel-arm, cluster-randomised controlled Hybrid Type II trial. 12 provincial health and administrative departments, each comprising 2–3 PHC centres—clusters—will be randomised in a 1:1 ratio to either the intervention or control (usual care) arm (figure 1). The trial will be conducted over 36 months and organised into three overlapping phases (figure 2). Phase I (9 months): Codesign, pilot testing the PHC care model’s refinement and associated implementation strategies. This phase will involve a pilot in two PHC centres, identification of barriers and iterative adaptation of the strategies. Phase II (30 months): Implementation of the trial. This phase includes a 9-month baseline data collection period, a 15-month intervention implementation period, and a 6-month follow-up in the intervention group to assess the sustainability of the implementation strategies. Phase III (6 months): Analysis, reporting and dissemination of findings. The study started on 1 November 2024 and ends on 31 October 2027.

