#### Study participants

The study population will include adult patients with T2D who receive care through the public healthcare system. Eligibility criteria are age ≥18 years, a confirmed diagnosis of T2D for at least 1 year, residency in Mendoza province and receipt of care at one of the participating PHC centres. We will construct a longitudinal cohort of 396 patients with T2D in both arms, enrolling patients before implementation and following them for 12 months for outcome assessment (e-Cohort).

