#### Sample size

Based on preliminary data from the diagnostic phase and published literature, the baseline rate of achievement for the composite primary outcome (glycaemic control (HbA1c <8%); blood pressure control (<140/90 mm Hg); and use of statins (statin prescription) -limited to patients ≥40 years-) in the control group is estimated at 30%. The intervention is expected to improve this to ≥50% (absolute effect size of 20%). We have calculated the sample size considering a parallel cluster randomised trial with a cohort design, including baseline and follow-up assessments. The trial is powered at 80% to detect an absolute difference of 20 percentage points between the control group (30%) and the intervention group (50%) on the composite primary outcome, assuming a two-sided significance level of 5%. The design includes six clusters per arm (12 in total) and accounts for the correlation structure of repeated measures using a two-period decay model. Specifically, we assumed an intracluster correlation coefficient (ICC) of 0.05, a cluster autocorrelation of 0.5, and an individual autocorrelation of 0.6. Standard errors were adjusted using a t-distribution to account for the small number of clusters. Based on these parameters, the required sample size before adjusting for attrition is 312 individuals (26 per cluster). Applying an attrition inflation factor of 1.25 (to allow for 20% loss to follow-up), the final sample size increases to 396 individuals (33 per cluster, 198 per arm).

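### The primary comparison is dated both at 12 months and at study end, and the sections disagree on whether controls are followed in the last 6 months

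*Protocol article*

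**What the plan says.** **Time of the primary comparison**

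- Data analysis compares the three components of the composite, the last being "statin uptake between the trial arms at the end of the study". The Abstract also places the primary comparison at study end.
- Study participants describes "enrolling patients before implementation and following them for 12 months for outcome assessment (e-Cohort").
- Data collection describes the cohort as drawn from both arms, "following them for 12 months for outcome assessment and an additional 6 months for sustainability assessment". The Abstract agrees: 12 months during the intervention, then 6 months of sustainment.
- Outcomes takes the primary outcome from routine clinical records.
- Data collection also says that the surveys "conclude with an endline questionnaire in person at the end of the intervention period".

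**Length of the periods, and who is followed**

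- Design divides Phase II (30 months) into 9 months of baseline, 15 months of intervention, and "a 6-month follow-up in the intervention group to assess the sustainability of the implementation strategies". It dates the end of the study at 31 October 2027.
- Phase III, Procedures, gives control clusters the package, if effective, only once follow-up has finished.
- Data analysis counts patients with missing clinical outcome data as not achieving the composite.

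**The concern.** The time of measurement is part of what the primary analysis estimates. A composite read at 12 months describes patients under active implementation. Read at the end of follow-up, it describes what remains after implementation has stopped. These are different effects, and the article attaches the primary analysis to both. Because the outcome comes from routine records, which exist at many dates, the same dataset can supply several versions of it. A team applying Data analysis and a team applying Study participants would extract different values.

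The second conflict makes the first more serious. If the last 6 months are followed only in the intervention group, a comparison dated at the end of follow-up has no planned concurrent control. The missing-data rule could then turn absent control data into control failures, which would favour the intervention. Sustainability, listed among the Phase III objectives, would become an uncontrolled before-after comparison.

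**Working it through.** **1. Time of the primary comparison.** Counting from the start of implementation:

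| Reading | Source | Month |
|---|---|---|
| Outcome assessment | Abstract, Study participants, Data collection | 12 |
| End of cohort follow-up | Abstract, Data collection: 12 + 6 | 18 |
| End of the sustainability period | Design: 15 + 6 | 21 |
| Calendar end of the study | Design | 31 October 2027, after the analysis phase |

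Study end could mean any of the last three rows, and none of them is month 12.

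**2. Do the durations fit together?** Phase II adds up: 9 + 15 + 6 = 30 months. The cohort follow-up does not: 12 + 6 = 18 against 15 + 6 = 21, a gap of 3 months.

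- If the 12 months start with implementation, the additional 6 cover months 12 to 18. Months 12 to 15 are still active intervention, so only 3 of the 6 months (15 to 18) fall in the sustainability period.
- If the additional 6 months are the sustainability period itself (months 15 to 21), the preceding 12 months run from month 3 to month 15. No section states that offset.

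**3. Who is followed in the last 6 months?** Design says the intervention group. Data collection says the cohort in both arms. The Abstract follows the full cohort of 396. Phase III, Procedures, keeps controls without the package until follow-up ends, which fits following both arms. As instructions for data collection, Design and Data collection differ.

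**4. What if Design governed and study end meant the end of follow-up?** Let u be the share of control patients with no outcome data at that time. Assume that u is unrelated to outcome and that the true control rate is the planned 30%. With missing scored as failure, the control rate becomes 0.30 × (1 − u): 30% at u = 0, falling to 0% at u = 1. Without that scoring, and at u = 1, no between-arm estimate exists. The article does not give u. It depends on whether control records are extracted in that window.

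**5. Does the timing affect the sample size?** Sample size states: "The trial is powered at 80% to detect an absolute difference of 20 percentage points". The inputs given there are 30% against 50%, two-sided 5%, 6 clusters per arm, ICC 0.05, cluster autocorrelation 0.5, individual autocorrelation 0.6, and m = 26 per cluster.

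- Variance inflation for clustering: 1 + (26 − 1) × 0.05 = 2.25.
- Correlation of cluster means between periods: r = (26 × 0.05 × 0.5 + 0.95 × 0.6) / 2.25 = 1.22 / 2.25 = 0.542.
- Design effect with baseline adjustment: 2.25 × (1 − 0.542²) = 1.588.
- Standard error: √[(0.3 × 0.7 + 0.5 × 0.5) / (6 × 26) × 1.588] = 0.0684.
- Noncentrality: 0.20 / 0.0684 = 2.92.
- Power: 79.8% with a t-distribution on 22 df (24 cluster-periods minus 2), which agrees with the stated 80%. With 10 df (12 clusters minus 2) it is 75.0%. The article does not state the df.
- Attrition: 26 / 0.8 = 32.5, rounded up to 33; 33 × 12 = 396, as stated.

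The calculation uses one undated follow-up, so the required number does not depend on the month chosen. As an illustration, assume that the 20% loss applies at 12 months and continues at a constant rate, so retention at month t is 0.8^(t/12):

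| Month | Loss | Patients per cluster | Power (22 df) |
|---|---|---|---|
| 12 | 20.0% | 26.4 | 80.0% |
| 15 | 24.3% | 25.0 | 79.1% |
| 18 | 28.4% | 23.6 | 78.2% |

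The timing changes power by less than 2 percentage points over this range.

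**The case against.** The strongest defence is that a sensible reader can resolve the text. The only explicit number attached to outcome assessment is 12 months. The phrase about study end cannot be a literal measurement date, because Design puts that date after the analysis. On controls, the clause in Design concerns sustainability of the implementation strategies, which exist only in intervention clusters, so it may describe implementation follow-up and leave the patient cohort untouched. Data collection and the Abstract follow the whole cohort, and controls stay without the package until follow-up ends. Losing the control group takes two unfavourable readings together. The exact record window may also be set in a plan that is not shown.

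Much of this stands, and it rules out three stronger readings that a reader might infer:

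- **Month 15 as a third primary time.** The documents do not say this. The end of the intervention is when the in-person questionnaire is given, and the primary outcome comes from clinical records.
- **Twelve months counted from enrolment.** With 9 months of baseline, this could leave an early enrollee with only 12 − 9 = 3 months of exposure. The Abstract places the 12 months during the intervention, which answers that reading.
- **A final period with no controls by design.** Design suggests this, but Data collection and the Abstract contradict it.

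The defence does not remove the contradiction. The section that defines the primary analysis uses the undated phrase, the Abstract uses both datings, and the 18 and 21 months remain unreconciled. An unseen analysis plan may supply detail, but the published text still states two times for one comparison.

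**Conclusion.** The point holds as an inconsistency that has to be resolved before the primary analysis is fixed. The primary comparison is dated at 12 months in some sections and at study end in others, where study end could mean month 18, month 21 or a calendar date after the analysis. The follow-up lengths differ by 3 months. The two sections that describe the last 6 months disagree on whether controls are included.

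Loss of the control group is conditional. It follows only if Design governs data collection and study end means the end of follow-up. It should be described as a risk, with scoring of unfollowed controls as failures as its worst form. It would be wrong to report that the trial lacks a control group at its primary time.

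The sample size is not affected: 312 and 396 reproduce (79.8% power, assuming 22 df and baseline adjustment), and the month chosen hardly changes power under the constant-loss assumption.

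**What to change.** 1. In the Abstract and in Data analysis, replace the reference to study end with one primary time. Twelve months after the implementation start date has the best support in the Abstract, Study participants and Data collection. Define the same calendar origin and the same record window for intervention and control departments, and use the same statement in all four places.
2. Reconcile Design with Data collection so that both arms are followed through the 6-month sustainability period.
3. State how the 12 + 6 months of cohort follow-up map onto the 15 + 6 months of intervention and sustainability.
4. Report any sustainability result as secondary.

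The cost is a wording amendment, plus record extraction in control clusters for the last 6 months, which Data collection already describes. No change to the sample size is needed.
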